### Acceptability Outcomes

Acceptability is operationalized as a multifaceted construct reflecting the degree to which participants consider *Gambling Habit Hacker* to be appropriate, based on their emotional and cognitive responses to the app [79]. Specifically, *intervention fidelity* will be assessed by the proportional response to EMA notifications, strategy selection, and completion of the written text for EMI action and coping plans. The content of each personalized action and coping plan will also be reviewed and rated: 0=not completed, 1=partially completed (ie, plan is created but is missing key detail on how or what the person will do right now), and 2=completed (ie, plan is created and includes all details as prompted). Subscales of the *Mobile App Rating Scale* [80] will be used to measure the subjective quality (4 items: willingness to recommend the app, future use, willingness to pay, and overall perception of quality) and perceived impact (6 items: awareness, knowledge, attitudes, intention to change, help seeking, and behavior change) of the app. *App use and engagement* will be assessed across the 28-day MRT and 6-month follow-up period by download information, onboarding information, app use information (eg, EMA compliance, intervention eligibility, participant retention, and intervention activities completed), and other evaluation information. A series of *semistructured interviews* will be conducted 28 days after trial with a subsample of 10 participants from the MRT. Participants will be selected based on gender and app use (high or low), with participants prioritizing the state of New South Wales in alignment with the funding source. Participants will be individually interviewed via videoconferencing and asked about their experiences with the *Gambling Habit Hacker* app as well as its perceived helpfulness and areas for improvement.

### Sample Size

A sample size of 200 will be recruited based on a conservative anticipated 40% attrition rate [52], providing a final sample of 120 at 6 months after evaluation. This sample size provides >85% power to detect a small binary outcome intervention effect of relative risk=1.20 (α=.05; availability parameter=0.3; randomization probability=.50; probability of outcome without intervention=.25) [81].

### Statistical Analyses

To assess the research questions, the method of generalized estimating equations will be used, with an appropriate link function for the outcome of interest (eg, logit or identity). Although an exchangeable working correlational structure is intended to be used for the analyses, considerations will be given to alternative correlational structures based on the observed within-person correlation pattern over the course of the study (eg, independent or auto-regressive). For all MRT analyses, the (lagged) outcome of interest (eg, adherence to expenditure limit at Time_t+1_) will be regressed on a variable denoting the treatment received (ie, intervention vs control) at Time_t_, as well as covariates (including unbalanced time). The primary analyses will explore the effect of intervention versus control on the probability of adherence to expenditure limits in the subsequent episode. The identification of the conditions under which the interventions are most beneficial and how the effect of the interventions changes over the course of the MRT will be examined by specifying interaction terms between the intervention variable and interaction variables of interest (eg, strength of intention and time).

The long-term outcomes of the intervention (within-group follow-up evaluation) will be explored, whereby distal outcomes will be assessed using generalized estimating equations by regressing the outcome of interest (eg, gambling expenditure) on a variable denoting time (ie, before intervention, after intervention, and 6-month follow-up) and covariates. The identification of factors predicting longer-term outcomes will also be assessed by regressing the outcome of interest (eg, clinically significant changes in gambling expenditure) with selected preintervention, postintervention, and app usage variables. Where appropriate, missingness will be addressed using multiple imputations with appropriate accounting for the multilevel nature of the data (eg, multilevel multiple imputation).

In addition to the effect sizes for all primary and secondary outcomes, the metrics of individual-level change will be calculated for all primary and secondary outcomes. Changes beyond that attributable to chance or measurement error will be evaluated using Reliable Change Indices [82], and clinically significant changes [83] will subsequently be calculated at postintervention and 6-month evaluation using functional score ranges where possible (G-SAS score of ≤20 and K6 score of ≤13) or at least a 25% improvement in scores [84]. Participants will be identified as *recovered* (final score falls into the functional range and corresponds to a reliable change), *improved* (final score corresponds to a reliable change but falls into the dysfunctional range), *unchanged* (final score does not correspond to a reliable change), or *deteriorated* (final score corresponds to a relative change in the negative direction).

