The primary aim of the 28-day MRT was to determine the efficacy of action- and coping planning versus control on goal adherence. Goal adherence is the primary proximal outcome and refers to adhering to gambling expenditure limits, which is operationalized as a binary outcome, with success defined as actual expenditure being no greater than 10% higher than the planned expenditure limit. Secondary proximal outcomes are strength of intention, goal self-efficacy, and urge self-efficacy. It is hypothesized that action- and coping planning interventions will be associated with higher rates of adherence to gambling expenditure limits compared with the control condition, as well as higher levels of strength of intention, goal self-efficacy, and urge self-efficacy. Should data allow, the secondary aims of this trial are to (1) determine how each of the following influences the intervention effect on adherence to gambling expenditure limits: time-variant (EMA) strength of intention, goal self-efficacy, urge self-efficacy or being in a positive or negative high-risk situation, alcohol or drug consumption, and gambling proximity and time-invariant factors measured before intervention, including age, gender, volitional phase, gambling symptom severity, gambling expenditure, and planning propensity and (2) explore whether the effect of the intervention on adhering to gambling expenditure limits changes over time as the treatment progresses over the course of the 28-day MRT.

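### The intended exchangeable working correlation can attenuate the proximal treatment effect if planning carries over; independence should be the primary structure, and the effect should be reported as a relative risk

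*Protocol article*

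**What the plan says.** Protocol article, Statistical Analyses: "Although an exchangeable working correlational structure is intended to be used for the analyses". Alternatives, with independent and autoregressive as examples, are to be considered according to the within-person correlation observed during the study. The model regresses adherence at the next occasion on treatment at the current one plus covariates, "with an appropriate link function for the outcome of interest (eg, logit or identity"). Moderation is examined through interaction terms.

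Research Aims and Hypotheses lists the time-varying moderators: "time-variant (EMA) strength of intention, goal self-efficacy, urge self-efficacy or being in a positive or negative high-risk situation", among others. Under Distal and Proximal Outcomes, intention and both self-efficacy items are also outcomes, read at the following EMA.

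Sample Size: "This sample size provides >85% power to detect a small binary outcome intervention effect of relative risk=1.20", with these inputs: "α=.05; availability parameter=0.3; randomization probability=.50; probability of outcome without intervention=.25".

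Two places bear on carry-over. Research Aims and Hypotheses posits that limits will be kept because intention and self-efficacy rise. The Discussion overview says the app lets users practise planning repeatedly, as a route to competence.

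**The concern.** With a working correlation that is not diagonal, the estimating equation contains products of treatment at occasion t and residuals at other occasions. Randomisation makes treatment at t independent of what came before it, so products with earlier residuals average to zero. It does not make treatment at t independent of what follows. If a plan made at t shifts later adherence, the products with later residuals do not average to zero, and the coefficient no longer estimates the proximal effect. A sandwich variance corrects the standard error, not this shift.

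The rule for changing the structure does not protect against this. It looks at how correlated the data are, not at whether the structure is valid for the estimand. Repeated measures on one person are usually correlated, so the rule would tend to keep a non-independence structure.

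At stake is a primary effect that is understated, in a trial with power only a little above 85%. A smaller point is the scale. The sample size is stated as a relative risk, while the two links given as examples yield an odds ratio or a risk difference, and the article does not say on which scale the primary effect will be reported.

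**Working it through.** **Stated power.** Inputs from Sample Size and the design: 200 recruited, 40% attrition, so 200 × 0.6 = 120; 3 × 28 = 84 decision points; availability 0.3; randomisation 0.5; 0.25 without intervention; RR 1.20, so 0.30 with it. Two-sided α of 0.05 is assumed.

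Available occasions: 120 × 84 × 0.3 = 3024, or 1512 per condition.

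| Scale | Effect | SE | Effect/SE | Power |
|---|---|---|---|---|
| Risk difference | 0.05 | √[(0.1875 + 0.21)/1512] = 0.01621 | 3.084 | 86.9% |
| log RR | ln 1.20 = 0.1823 | √[(3 + 2.333)/1512] = 0.05939 | 3.070 | 86.7% |
| log OR | ln[(0.30/0.70)/(0.25/0.75)] = ln 1.286 = 0.2513 | √[(5.333 + 4.762)/1512] = 0.08171 | 3.076 | 86.8% |

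Power is Φ(effect/SE − 1.96). The protocol's figure is reproduced, and the choice of link does not move it.

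**Exchangeable versus independence.** Large-sample simulation: 20,000 to 40,000 persons, 84 decision points, availability 0.3, 50:50 randomisation, true proximal risk difference 0.05, identity link. Carry-over size and between-person variance are assumptions, because the article gives neither.

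| Scenario | Independence | Exchangeable | Difference |
|---|---|---|---|
| No carry-over | 0.0516 | 0.0515 | none |
| Eligibility depends on earlier responses, no carry-over | 0.0498 | 0.0501 | none |
| Fading carry-over, moderate | 0.0514 | 0.0493 | −4% |
| Fading carry-over, larger | 0.0512 | 0.0472 | −8% |
| Cumulative carry-over | 0.0508 | 0.0438 | −14% |
| Cumulative, larger between-person variance | 0.0508 | 0.0415 | −18% |

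Logit fits moved in the same direction (cumulative: log OR 0.2549 versus 0.2196). With no true proximal effect but fading carry-over, exchangeable gave −0.003 and independence 0.001.

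**Check by hand.** For the identity link with m randomised occasions and working correlation ρ, the exchangeable inverse is proportional to I − c·11ᵀ, with c = ρ/[1 + (m − 1)ρ]. Suppose intervention rather than control at one occasion shifts every later outcome probability by δ. The expected shift in the estimate is then approximately −[c/(1 − c)] × δ × (m − 1)/2. Under independence c = 0 and the shift vanishes. Here m = 84 × 0.3 = 25.2, so (m − 1)/2 = 12.1.

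- Cumulative case: each past intervention occasion added 0.05/4 = 0.0125 and each control occasion removed it, so δ = 0.025. Fitted ρ = 0.054 gives c = 0.054/2.307 = 0.0234 and c/(1 − c) = 0.0240. Shift = 0.0240 × 0.025 × 12.1 = 0.0073, so 0.0508 − 0.0073 = 0.0435 (simulated 0.0438).
- Larger between-person variance: ρ = 0.121 gives c/(1 − c) = 0.0318. Shift = 0.0318 × 0.025 × 12.1 = 0.0096, so 0.0412 (simulated 0.0415).
- Milder case, ρ = 0.07, so c/(1 − c) = 0.0267: δ = 0.002 gives 0.0006 (about 1% of 0.05) and δ = 0.01 gives 0.0032 (about 6%). A simulation at these sizes gave about 1% to 6%, and under 1% for fading carry-over that halves at each occasion.

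The two upper rows therefore assume a lasting effect of δ/0.05 = half the immediate effect, which is large.

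**Consequence for power.** At 0.25 versus 0.294, SE = √[(0.1875 + 0.2076)/1512] = 0.01616 and 0.044/0.01616 = 2.72, so power is about 78%.

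**Moderators.** Where the moderator depended on earlier outcomes, the treatment-by-moderator term barely moved between exchangeable and independence: 0.0540 versus 0.0544, 0.1028 versus 0.1029, and 0.0479 versus 0.0477. The moderator's own main effect did move (for example 0.126 versus 0.164).

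**The case against.** The strongest reply is that the problem is conditional. With constant 50:50 randomisation and no carry-over the two structures agree, and eligibility that depends on earlier responses does not by itself separate them. The article gives no carry-over size, and the plans are designed around immediate threats, so effects may fade fast and the gap may be 1% or less. Independence is already among the alternatives named. The links are introduced as examples across binary and scaled outcomes, so a log link is not excluded, and a logit fit can be standardised to a relative risk. The shift seen is towards a smaller effect, so it does not flatter the intervention. Centring, weighting and small-sample corrections may be settled in an analysis plan that is not shown.

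Most of this stands, and it limits the point to a possible bias of uncertain size. It does not remove it. Exchangeable is the published default, and naming independence as an option gives little protection when the selection criterion is observed correlation.

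A reader might infer that the planned analysis is biased as such, or that power is computed for an effect the model cannot estimate. The documents support neither: the first needs carry-over, and the second treats examples as a fixed choice.

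**Conclusion.** The point holds in conditional form. If planning at one occasion affects adherence at later ones, the exchangeable default can attenuate the proximal effect, by about 1% to 18% over the carry-over sizes tried and not at all without carry-over. The upper end rests on strong, lasting carry-over and marked between-person variance, both assumed. Selecting the structure by observed correlation offers no safeguard.

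A reader might also infer that the moderator analyses are biased more than the main effect. That is not established. One small simulation (30 to 60 replicates per scenario) showed treatment-by-intention coefficients 14% to 23% lower under exchangeable, but the large-sample runs did not reproduce it. What they did reproduce is a shift in the moderator's main effect, which is not an effect that the trial sets out to estimate. Other mechanisms could behave worse, so this is not proof of safety.

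The scale mismatch concerns reporting only. RR 1.20 from 0.25 is the same alternative as RD 0.05 or OR 1.29, and power is about 87% on all three scales.

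**What to change.** For the proximal-outcome analyses of the microrandomized trial:

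- Make independence working correlation primary, or an equivalent centred estimator for this design. Restrict it to randomised occasions and use person-clustered robust standard errors.
- Keep exchangeable and autoregressive structures as sensitivity analyses, and drop the rule that lets the observed correlation choose the primary structure.
- State that the primary effect will be reported as a relative risk, from a log link or standardised from a logit fit, to match Sample Size.

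The cost is a few sentences and standard software, with no new data and no change in sample size. The downside is slightly wider intervals in some scenarios: in the small simulation the standard deviation of the treatment estimate was 0.079 under independence and 0.075 under exchangeable.

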## Methods

### Trial Design

A 28-day MRT will be used to facilitate the optimization of *Gambling Habit Hacker*. In this trial, *decision points* comprise notifications that participants will receive via their smartphones to complete a time-based EMA 3 times a day. In each EMA, *tailoring variables*, including strength of intention, goal self-efficacy, urge self-efficacy, and high-risk situations, are used to determine intervention eligibility according to *decision rules* based on EMA cutoff points. At each decision point, participants will be randomly allocated to either the intervention or a control condition (*intervention options*). This MRT will evaluate the JITAI entirely as a *push* intervention.

This MRT will be supplemented with (1) a 6-month within-group follow-up that explores the long-term impact of the app on gambling expenditure (primary distal outcome) and a range of secondary outcomes (gambling frequency, gambling symptom severity, psychological distress, well-being, situational confidence, and planning propensity) as well as the predictors of longer-term treatment outcomes and (2) an evaluation of the acceptability of the JITAI via postintervention surveys, app use and engagement indices, and semistructured interviews.

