The primary outcome for the within-group evaluation will be gambling expenditure (measured using a TimeLine Follow-Back at the preintervention evaluation, the EMA data collected during the intervention period and amalgamated for the posttreatment evaluation, and single items at the 6-month evaluation). Secondary outcomes will include gambling symptom severity measured using the G-SAS [57], gambling frequency with the TimeLine Follow-Back at the preintervention evaluation (EMA data at the posttreatment evaluation and single items at the 6-month evaluation) [74], psychological distress measured using the Kessler 6 Psychological Distress Scale [75], personal well-being measured using the Personal Wellbeing Index [76], the Brief Situational Confidence Questionnaire [77], and planning propensity measured using an adapted action control questionnaire that assesses action planning, coping planning, and action control [78]. A summary of the measures and the measurement time points (before intervention, after intervention, and follow-up) for the within-group evaluation are presented in Multimedia Appendix 2.

To enhance engagement with the posttreatment and 6-month follow-up evaluations, the following protocols will be implemented. An email will be sent to all participants to prompt survey completion, with a second reminder email for those who fail to complete within a week. An advance notice email will also be sent a week before the 6-month surveys are administered. For those who have not completed the survey after a further week, up to two reminder telephone calls will be made by a clinical or qualitatively trained researcher. At each time point, the option to complete the survey over the phone with a trained research fellow will be offered. Participants who do not complete posttreatment evaluation will be contacted at the 6-month evaluation unless they have withdrawn from the study.

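### The 25% improvement fallback for clinically significant change is ill-suited to well-being, situational confidence and planning propensity: on bounded scales it has a ceiling and depends on where zero is coded

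*Protocol article*

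**What the plan says.** The Statistical Analyses section states that "the metrics of individual-level change will be calculated for all primary and secondary outcomes". Reliable Change Indices come first. Clinically significant change is then derived, at postintervention and at 6 months, from "functional score ranges where possible (G-SAS score of ≤20 and K6 score of ≤13) or at least a 25% improvement in scores". For an outcome without a functional range, only the last part applies: "or at least a 25% improvement in scores".

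The secondary outcomes listed under Trial Design include "psychological distress, well-being, situational confidence, and planning propensity". Within-Group Evaluation names the instruments: "personal well-being measured using the Personal Wellbeing Index", "the Brief Situational Confidence Questionnaire" and "planning propensity measured using an adapted action control questionnaire that assesses action planning, coping planning, and action control". The article gives no functional range for the last three outcomes in that list, and no scoring range, direction or item coding.

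Four classes follow. *Recovered* needs a reliable change and a final score in the functional range. *Improved* needs a reliable change with a final score still in the dysfunctional range. *Unchanged* means no reliable change, and *deteriorated* means change in the wrong direction. The 25% rule is not written into any of the four.

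**The concern.** Change metrics are promised for every primary and secondary outcome, and only two instruments have a functional range. The 25% rule is therefore the stated criterion for the rest. For gambling expenditure and frequency, where zero means none and improvement is a fall, a percentage of baseline has a clear meaning. Well-being, confidence and planning scores would ordinarily run upward to a fixed top. There, a percentage of one's own starting score has a ceiling, asks more of people who start higher, and changes with an arbitrary choice of zero.

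At stake is the reported share with clinically significant change on three secondary outcomes of an uncontrolled within-group follow-up. That share would partly reflect baseline position and item coding rather than change.

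**Working it through.** The protocol reports no figure on this point, so there is nothing to reproduce. The 25% threshold, the use of the Reliable Change Index and the list of outcomes come from the article. Everything else is assumed: percentage relative to baseline, higher is better, a fixed maximum and, for the shares, a 0-100 scale with normally distributed baselines. The means, SDs and reliabilities are illustrative.

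**1. Ceiling.** A 25% gain from baseline b on a scale with maximum U needs 1.25 × b ≤ U, so b ≤ U/1.25 = 0.8U. The highest baseline that can qualify is 80 on 0-100, 8 on 0-10, 4 on 1-5 and 5.6 on 1-7.

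**2. Sliding requirement.** The gain needed is 0.25 × b: 5 points from a start of 20, and 19 points from a start of 76.

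**3. Zero point and direction.** A gain of 0.6 from 3.0 to 3.6 on 1-5 coding is 0.6/3.0 = 20% (fails). The same answers coded 0-4 go from 2.0 to 2.6, and 0.6/2.0 = 30% (passes). On 0-100, a move from 60 to 70 is 10/60 = 16.7% (fails). Reverse-scored, it is 40 to 30, and 10/40 = 25% (passes).

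**4. Reliable change for comparison.** The minimum reliable change is 1.96 × √2 × SD × √(1 − reliability). It is one number of points for everyone, and the index does not change under linear recoding. It has its own ceiling, at 100 minus that number. The share shut out by the 25% ceiling alone is therefore the share with a baseline between 80 and (100 − minimum reliable change).

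| Mean, SD | Above 80 | Min. reliable change (.90) | Reliable-change ceiling (.90) | Shut out by 25% alone (.90) | Min. reliable change (.80) | Reliable-change ceiling (.80) | Shut out by 25% alone (.80) |
|---|---|---|---|---|---|---|---|
| 50, 20 | 6.7% | 17.5 | 82.5 | 1.5% | 24.8 | 75.2 | 0 |
| 60, 20 | 15.9% | 17.5 | 82.5 | 2.8% | 24.8 | 75.2 | 0 |
| 70, 15 | 25.2% | 13.1 | 86.9 | 12% | 18.6 | 81.4 | 2.9% |
| 75, 12 | 33.8% | 10.5 | 89.5 | 22% | 14.9 | 85.1 | 14% |

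**5. Below the ceiling.** The 25% rule asks for more than reliable change when 0.25 × b exceeds the minimum reliable change, that is, when b exceeds four times that number. At reliability .90 this is above about 53 for SD 15 (13.1/0.25), 42 for SD 12 and 70 for SD 20. At SD 20 and reliability .80 it is above 99, beyond the rule's own ceiling, so at every baseline that could meet 25% the rule is no stricter than reliable change.

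**The case against.** The strongest reply has four parts.

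**The classes.** A reader might infer that people who start high can never be classed as improved. The text does not support that. *Improved* rests on reliable change and carries no 25% condition, and the split between reliable and unreliable change does not move under linear recoding. At most, the 25% rule can withhold the clinically significant label (or *recovered*, if 25% is meant to stand in for a functional range, which the article does not say). This stands.

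**Order of steps.** A reader might also fear that 25% used alone would credit noise in low scorers, since a small absolute gain suffices there. But reliable change is evaluated first and the clinically significant step comes after it, so the text gives little reason to expect that use.

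**Size.** It is tempting to read the shares above 80 (about 7% to 34%) as the damage done by the rule. Much of that group could not show a reliable gain either. At SD 20 and reliability .80, reliable change fails from 75.2 upward, so it excludes more high starters than the 25% rule does (10% against 7% at mean 50; 22% against 16% at mean 60). This stands, and the smaller shares are the ones to use.

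**Undocumented premises.** The article does not give the scales' range or direction, nor say that 25% is of baseline rather than of scale range. On 0-100, a quarter of the range would be a fixed 25 points, with a ceiling at 75 and no dependence on coding. Further functional ranges could also be set elsewhere. These points make the conclusion conditional. They do not remove it, because percentage of baseline is the ordinary reading and the rule as published covers these outcomes.

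Predictor models are a further tempting step: baseline would predict a percentage-based class by arithmetic. The article's only example of such a model concerns expenditure, so for these three scales the harm is speculative.

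**Conclusion.** The point holds in a limited form. As written, the 25% rule is the criterion for clinically significant change on three outcomes for which a percentage of baseline is a poor measure. On the assumptions of bounded scores, higher being better and a percentage of baseline, it is unreachable above 80% of the maximum, demands more of higher starters, and can give opposite verdicts on identical answers under different codings.

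The share shut out by its ceiling beyond what reliable change already excludes is about 1.5% to 22% at reliability .90 and 0 to 14% at .80 in the scenarios shown. It can also be the stricter test at attainable baselines, for example above about 53 at SD 15 and reliability .90. With a wide SD and lower reliability it adds almost nothing.

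These metrics supplement the effect sizes and the generalized estimating equation analyses, and the microrandomized primary analysis is untouched. Severity is minor.

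**What to change.** In Statistical Analyses, confine the 25% criterion to gambling expenditure and gambling frequency. For the Personal Wellbeing Index, situational confidence and planning propensity, classify on the Reliable Change Index alone, which is already planned, and report mean change in scale points or baseline SDs.

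The cost is one sentence and no new data. Three secondary outcomes lose a clinically significant label, and reliable change keeps a ceiling of its own, which should be acknowledged when results for high starters are read.

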### Participant Eligibility and Recruitment

Participants will be recruited using a range of strategies, such as web-based advertising, social media, gambling-related websites, and advertisements in public places such as mental health and addiction services, general practices, and universities. Gambling counseling services and gaming venues across Australia and New Zealand may also assist in participant recruitment. The eligibility criteria are (1) current Australian or New Zealand residence, (2) aged ≥18 years, (3) able to install an app on their own smartphone with internet access, (4) willing to have app notifications activated, (5) English fluency, and (6) seeking assistance for their own gambling. The target population is those with less severe gambling problems who want to adhere to their gambling expenditure limits through the promotion of the app. Consistent with a pragmatic design, there is no requirement to meet any problem gambling diagnostic criteria, and participants are able to engage in other help-seeking activities [56]. However, we will measure the severity of gambling problems using the Gambling Symptom Assessment Scale (G-SAS) [57] to determine the gambling symptom severity of gamblers using the app and explore the degree to which gambling symptom severity influences the efficacy of the intervention.

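### The *recovered* category does not require a dysfunctional pre-intervention score, so participants already in the functional range on the G-SAS or K6 can be reported as recovered

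*Protocol article*

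**What the plan says.** The last paragraph of Statistical Analyses sets out individual-level metrics for all primary and secondary outcomes, calculated after the intervention and at 6 months. "Changes beyond that attributable to chance or measurement error will be evaluated using Reliable Change Indices". Clinically significant change is then judged by "functional score ranges where possible (G-SAS score of ≤20 and K6 score of ≤13") or, as the alternative, by "at least a 25% improvement in scores".

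Four labels follow, offered as alternatives:

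- *recovered*: "final score falls into the functional range and corresponds to a reliable change"
- *improved*: a reliable change here too, with the participant still ending outside the functional range
- *unchanged*: no reliable change
- *deteriorated*, which is worded differently from the other three: "final score corresponds to a relative change in the negative direction"

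Under Participant Eligibility and Recruitment, "there is no requirement to meet any problem gambling diagnostic criteria", and the app is aimed at people with less severe problems. Under Within-Group Evaluation, the baseline question on volitional phase includes an option for people who have already changed their gambling and want to maintain that change.

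**The concern.** Recovery implies moving from the dysfunctional to the functional range. The stated rule tests only where a participant ends and whether the change was reliable. It does not test where the participant began. In a trial that required scores above the cut-off at entry, the omission would be harmless. Here no such requirement exists, for gambling severity or for psychological distress, so some participants can be expected to start at or below a cut-off.

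At stake are the recovery proportions on the G-SAS and K6 after the intervention and at 6 months. They come from an uncontrolled within-group evaluation, so no comparison group would reveal that some of those counted as recovered had never been above the cut-off.

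**Working it through.** The article gives no figure for these categories, so there is none to reproduce. The check applies the rules to score pairs and then gauges the size under assumptions.

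**1. The rules applied to G-SAS score pairs.** The cut-off of 20 is from the article. The 10-point threshold for reliable change is assumed.

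| Before → after | Categories met as worded |
|---|---|
| 32 → 15 | recovered (as intended) |
| 40 → 27 | improved (as intended) |
| 18 → 6 | recovered, though never above 20 |
| 15 → 30 | improved and deteriorated |
| 4 → 16 | recovered and deteriorated |

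The third row is the point at issue: only one category applies, it is the wrong one, and nothing else in the section corrects it. The last two rows concern wording and are taken up under the objection.

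**2. Threshold for reliable change.** Threshold = 1.96 × SD × √(2(1 − r)). The article gives neither SD nor reliability r, so both are assumed.

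- G-SAS, set A (SD 9, r 0.85): 1.96 × 9 × √0.30 = 9.7 points.
- G-SAS, set B (SD 10, r 0.87): 1.96 × 10 × √0.26 = 10.0 points.
- K6, set A (SD 5, r 0.85): 1.96 × 5 × √0.30 = 5.4 points.
- Over SD 8–12 and r 0.80–0.95, the G-SAS threshold runs from about 5 to 15 points.

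**3. Share of recovered cases already functional at baseline.** This was simulated with 400,000 participants per scenario, and *recovered* was read as requiring improvement. Scores were held to assumed scales of 0–48 (G-SAS) and 0–24 (K6). Set A builds scores from a true score plus error, with mean true improvement 4 (SD 6) on the G-SAS and 2 (SD 3) on the K6. Set B uses a pre–post correlation of 0.6 and a mean drop of 0 or 6 points.

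| Scale and set | Baseline mean | Share already functional |
|---|---|---|
| G-SAS, A | 18 / 22 / 26 | 49% / 36% / 24% |
| G-SAS, B | 16 / 20 / 24 / 28 | 36–42% / 24–30% / 16–19% / 9–12% |
| K6, A | 7 / 10 / 13 | 80% / 64% / 45% |

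**4. Effect on the proportion recovered, with everyone in the denominator.** Set B, mean drop 6:

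| Baseline mean | At ≤20 at baseline | Recovered, no baseline condition | Recovered, dysfunctional baseline required | Same cases ÷ those dysfunctional at baseline |
|---|---|---|---|---|
| 16 | 66% | 27.0% | 15.8% | 15.8/34 = 46% |
| 20 | 50% | 27.0% | 19.0% | 19.0/50 = 38% |
| 24 | 34% | 24.6% | 19.9% | 19.9/66 = 30% |
| 28 | 21% | 20.1% | 17.7% | 17.7/79 = 22% |

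In set A the fall is from 19.8% to 10.1% for the G-SAS at mean 18, and from 16.7% to 6.0% for the K6 at mean 10. For the 120 participants expected at 6 months, the set B row with mean 20 gives 0.270 × 120 ≈ 32 against 0.190 × 120 ≈ 23 labelled recovered.

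Adding the condition can only lower the count. The last column shows that a rate among those at risk need not be lower than the rate now reported. It has a different denominator and answers the intended question.

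**5. What does not move.** Reliable improvers removed from *recovered* join *improved*, so the two categories together hold the same people before and after the change.

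**The case against.** The strongest reply is that these people did improve reliably. A reliable drop needs a score to fall from: at a threshold of 9.7 points, someone starting at or below 20 on the G-SAS must have started at about 10 or more. All participants are also seeking help for their gambling. This stands. It would be wrong to call such participants symptom-free. The label is wrong, but the benefit is not invented.

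A reader might also infer that worsened participants can be counted as successes, because *recovered* and *improved* state no direction. The document does not support that reading. The labels themselves, the 25% improvement criterion and the separate *deteriorated* category, which is tied to negative change, all show the intent. Every reliably worsened participant also meets *deteriorated*. Even on the strictly literal reading, set A puts only about 3–4% of the sample in the G-SAS *improved* group and 0.2–0.8% in *recovered* through worsening. What remains is a drafting gap: the categories overlap and no precedence is given. Similarly, *deteriorated* speaks of relative change where the other three say reliable. This is probably a slip, but read literally it makes a small worsening both *unchanged* and *deteriorated*.

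Finally, the article is condensed and cites method papers that may supply the baseline condition. That cannot be checked here. However, the article does not defer the definition: it spells out all four categories, and an analyst following them would omit the condition.

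**Conclusion.** The concern holds for the missing baseline condition. As written, the rule labels reliable improvers who were already at G-SAS ≤20 or K6 ≤13 as recovered, and it overstates the number recovered. That the error can occur follows from the text alone. Its size does not: the 9–49% (G-SAS) and 45–80% (K6) shares rest on assumed SDs, reliabilities, baseline means and changes, and they shrink as baseline severity rises.

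The reach is limited. Functional ranges are stated only for two secondary outcomes, and the metrics supplement the effect sizes in the within-group evaluation. The primary microrandomized comparison, the power statement and the combined recovered-or-improved proportion are untouched. The correction is worth making before results are classified, but it does not threaten the trial's main conclusion.

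**What to change.** Reword the four categories in Statistical Analyses:

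- *Recovered*: pre-intervention score in the dysfunctional range, reliable change in the direction of improvement, and final score in the functional range.
- *Improved*: any other reliable change in the direction of improvement.
- *Deteriorated*: reliable change in the direction of worsening, replacing the reference to relative change.
- *Unchanged*: no reliable change.

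Report *recovered* with the number dysfunctional at baseline as the denominator, and state that number for each scale. The four categories are then mutually exclusive.

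The cost is wording only, since all the scores are already collected. Fewer participants will be labelled recovered, and the smaller denominator makes the recovery estimate less precise, particularly on the K6 if most participants start at or below 13.
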